### Reference standard adjudication

2.5

The reference standard will be an adjudicated standardized CRS-R score generated by a three-member expert committee composed of senior clinicians experienced in DoC assessment. The committee will review a de-identified package containing synchronized video recordings when available, structured bedside observation forms, nursing observations within the surrounding 12-h window, medication and airway records, body-position records, confounder documentation, and other behaviorally relevant clinical notes.

Each expert will independently rescore the CRS-R at item and subscale level according to standard CRS-R administration and scoring rules. The adjudicated reference score will not be an expert modification of CRS-R scoring. Instead, the committee will identify the highest CRS-R-consistent response observed across paired assessments and supporting records after excluding responses judged artifactual, reflexive, or confounded by temporary clinical factors.

For this protocol, a response will be considered reproducible when it is observed more than once within the paired assessment record, is corroborated by video or structured bedside documentation, or is confirmed by consensus review as a stable response pattern rather than an isolated artifact. A response will be considered behaviorally credible when it is temporally linked to the relevant CRS-R stimulus or command, is compatible with the patient's motor and sensory capacities, and cannot be better explained by reflex activity, startle, seizure activity, airway manipulation, sedation fluctuation, or another documented confounder. If independent expert scores differ by more than 2 total points or produce different diagnostic categories, a consensus meeting will be held. If disagreement remains unresolved and the participant is clinically stable, an additional senior bedside assessment within 24 h may be used as a tie-breaker.

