### Study design and setting

2.1

This is a two-stage study consisting of retrospective model development followed by prospective, blinded clinical validation. The study will be conducted at Guangdong Second Traditional Chinese Medicine Hospital. The clinical research unit named in the ethics approval is Guangdong Second Traditional Chinese Medicine Hospital, with implementation through the Department of Acupuncture and Rehabilitation, Huangpu Hospital District.

The primary aim is to determine whether AI-standardized CRS-R total scores show smaller absolute error than unstandardized bedside CRS-R total scores when compared with an adjudicated standardized reference. The secondary aims are to assess subscale-level agreement, diagnostic-category agreement, inter-rater variability, uncertainty-flag performance, workflow feasibility, and exploratory day-14 consciousness improvement.

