#### Rater training, standardization, and blinding

2.4.1

Bedside raters will be rehabilitation physicians or therapists who have completed structured CRS-R training before study initiation. Before formal enrollment, raters will complete a study-specific rater standardization phase including manual review, practice scoring, and pilot paired assessments in non-study cases. Raters must demonstrate substantial agreement during the pilot phase before participation.

For each participant, two bedside raters will be blinded to each other's scores and to AI output. EEG readers will be blinded to CRS-R scores and AI output. The adjudication committee will be blinded to rater identity, raw AI output, and model explanation results. The statistical team will analyze a de-identified dataset after database lock.

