#### Assessment workflow

2.4.2

Each participant will undergo a prespecified assessment episode. The target workflow is completion of both CRS-R assessments and the EEG recording during the same morning block and before acupuncture, neuromodulation, or intensive rehabilitation sessions. The target interval between the two CRS-R assessments is no more than 2 h, and the target EEG timing is within 2 h before or after the midpoint of the paired CRS-R assessments. If target timing is not feasible, the maximum permitted interval will be 4 h between the two CRS-R assessments and 6 h between EEG and the paired CRS-R assessment window. Reasons for exceeding the target interval will be recorded. Sedation changes, fatigue, nursing care, airway events, acute complications, and rehabilitation sessions occurring within the assessment window will be recorded and used in sensitivity analyses.

The workflow will include:

Eligibility confirmation and consent from the legally authorized representative.Collection of baseline demographic and clinical contextual variables.First bedside CRS-R assessment by rater A.Second independent bedside CRS-R assessment by rater B, with a target interval of no more than 2 h and a maximum interval of 4 h after the first assessment.Routine scalp EEG, with a target timing within 2 h of the midpoint of the paired CRS-R assessments and a maximum timing within 6 h of the paired assessment window.Video recording of bedside behavioral assessments when consent and local policy permit.Offline AI inference using each rater's raw CRS-R subscale scores, EEG data, and clinical contextual data.Blinded expert adjudication to generate the standardized reference CRS-R score and diagnosis.

The order of raters will be alternated when operationally possible. Major medication, sedation, body-position, ventilatory, arousal-state, fatigue, nursing-care, treatment-session, or acute-complication changes between ratings will be documented. Participants with major instability between raters will remain in feasibility summaries and may be excluded from prespecified sensitivity analyses.

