### Outcome measures

2.7

The primary outcome is the participant-level reduction in absolute CRS-R total-score error after AI-assisted standardization. For rater *j* of participant *i*, raw and AI-standardized absolute error, and participant-level paired difference are defined in Equations 1, 2, and3, respectively.

$$\begin{array}{l} \Delta_{ij}^{\text{raw}}=|T_{ij}^{\text{raw}}-T_{i}^{\text{ref}}|, \end{array}$$
(1)

$$\begin{array}{l} \Delta_{ij}^{\text{AI}}=|{\hat{T}}_{ij}-T_{i}^{\text{ref}}|, \end{array}$$
(2)

where $T_{i}^{\text{ref}}$ is the adjudicated reference total score.

The participant-level paired difference will be:

$$\begin{array}{l} D_{i}=\frac{1}{2}\overset{2}{\underset{j=1}{\sum }}\left(\Delta_{ij}^{\text{raw}}-\Delta_{ij}^{\text{AI}}\right). \end{array}$$
(3)

The primary analysis will test whether the mean of *D*_*i*_ differs from zero, with positive values indicating error reduction after AI-assisted standardization. This definition aligns the endpoint with the participant-level recruitment target while preserving both rater-specific observations.

Secondary outcomes include mean absolute error, root mean square error, agreement between AI-standardized and reference diagnostic category, agreement between standardized and reference subscale scores, reduction in inter-rater variability, sensitivity and specificity for detection of MCS and emergence from MCS, macro-averaged F1-score, uncertainty-flag performance, workflow feasibility, and exploratory consciousness improvement at day 14. Consciousness improvement will be defined as at least one ordered diagnostic-category improvement by day 14 compared with baseline. CRS-R total-score change at day 14 will be analyzed as a sensitivity metric. Discharge status and discharge timing will be reported descriptively rather than used as a primary prognostic time point.

Inter-rater variability for raw and AI-standardized total scores is calculated as specified in Equations 4 and 5.

$$\begin{array}{l} V_{i}^{\text{raw}}=|T_{i1}^{\text{raw}}-T_{i2}^{\text{raw}}|, \end{array}$$
(4)

$$\begin{array}{l} V_{i}^{\text{AI}}=|{\hat{T}}_{i1}-{\hat{T}}_{i2}|. \end{array}$$
(5)

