Several design features are intended to reduce avoidable bias. Paired independent CRS-R assessments will allow direct comparison between raw inter-rater variation and post-standardization agreement. Blinding of bedside raters, EEG readers, adjudicators, and the statistical team should limit expectation effects and incorporation bias. The adjudicated reference will integrate structured behavioral observations, available video, nursing observations, medication exposure, airway status, body position, and other confounders, reflecting the clinical reality that a single bedside score may not capture the highest reproducible behavior. This design is aligned with SPIRIT-AI principles, which emphasize transparent reporting of intervention components, human-AI interaction, handling of errors, and procedures for monitoring algorithm performance (33).

The study has limitations. It is single-center, and its findings may be influenced by local patient mix, EEG equipment, assessment culture, rehabilitation workflow, and adjudication practice. The reference standard is expert-adjudicated but still behaviorally anchored, and it cannot fully resolve covert consciousness detected only by specialized task-based neuroimaging or electrophysiology (2, 4, 6). Video availability may vary according to consent and local policy. EEG artifacts and clinical instability are expected in this population, and fallback to report-level EEG variables may reduce model precision. Finally, because the system will operate in read-only mode, this validation study will assess standardization accuracy, feasibility, and safety signals, not whether AI-assisted scoring improves downstream treatment decisions or patient outcomes.

If successful, the study may provide a reproducible framework for human-supervised AI-assisted CRS-R score standardization. Its most plausible near-term role would be to flag cases requiring repeat assessment, expert review, or closer scrutiny of confounding conditions, particularly when model uncertainty is high or when standardized scores differ substantially from raw bedside scores. Such a use case would be consistent with the current maturity of EEG-based and AI-based approaches in DoC, where decision support and standardization are more defensible than autonomous diagnosis (1, 5, 30).

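### The reference is drawn from the same two assessments that supply the comparator and the AI input, so a positive mean D_i does not show that EEG contributes

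*Protocol article*

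**What the plan says.** Four parts of the protocol article fit together here.

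- **Reference (2.5).** Three experts rescore each case, and "the committee will identify the highest CRS-R-consistent response observed across paired assessments and supporting records". The sentence goes on to limit this rule: "after excluding responses judged artifactual, reflexive, or confounded by temporary clinical factors". The supporting records include nursing observations from the surrounding 12 hours.
- **Comparator (2.1, 2.7).** The primary aim asks whether AI totals have smaller absolute error than "unstandardized bedside CRS-R total scores when compared with an adjudicated standardized reference". Equation 1 takes each single rater's raw total from the same paired assessments. D_i averages, over the two raters, raw error minus AI error, and its mean is tested against zero.
- **AI input (2.4.2).** The workflow lists "Offline AI inference using each rater's raw CRS-R subscale scores, EEG data, and clinical contextual data".
- **Blinding (2.4.1, Discussion).** "The adjudication committee will be blinded to rater identity, raw AI output, and model explanation results". The bedside records themselves are not masked, since they are what the committee reviews. The Discussion then states: "Blinding of bedside raters, EEG readers, adjudicators, and the statistical team should limit expectation effects and incorporation bias".

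The one ablation planned in 2.10 is a reduced mode that keeps report-level EEG variables. No comparator without EEG is described.

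**The concern.** The raw comparator is one rating. The reference is close to the better of two ratings, one of which is that same rating, with further records added. A gap in one direction is therefore expected before any AI is applied. A rule that only moves raw scores upward can close part of that gap without using EEG.

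The study objective is a system that integrates EEG with bedside scores and clinical context. If the primary result is positive, readers will tend to credit the EEG component. Nothing planned would tell them whether that is right. Blinding the committee to AI output keeps that output from influencing the reference, but it does not touch the information that reference, comparator and AI input share.

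**Working it through.** **Inputs.** From the documents: six subscales (2.3.4), two raters, the rules in 2.5 and 2.7, and in 2.9 an assumed mean reduction of 1.0 point and 98 evaluable participants. The plan gives no rating noise, rejection rate or expected offset, so there is no plan figure to reproduce, and the 1.0 point serves only as a benchmark. Rating noise, rejection rates and subscale maxima (4, 5, 6, 3, 2, 3) are assumptions below.

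**Step 1: direction.** If no response is rejected, the reference on each subscale is at least the larger of the two ratings. Then T_ref is at least T_raw for both raters. Rejections pull T_ref down; supporting records can push it up.

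**Step 2: one-level discrete errors.** Suppose each rater independently misses one level on a subscale with probability p, with no over-scoring and no rejections. A rater falls short of the reference on a subscale when that rater misses and the other does not, with probability q = p(1 − p). With k subscales on which a miss is possible, the shortfall X is binomial(k, q). Adding 1 point to every raw total gives

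mean D = E(X) − E|X − 1| = 1 − 2·P(X = 0) = 1 − 2(1 − q)^k.

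- p = 0.1, k = 6: 1 − 2(0.91^6) = −0.14, so the best shift is none and D = 0.
- p = 0.2, k = 6: 1 − 2(0.84^6) = 0.30.
- p = 0.3, k = 6: 1 − 2(0.79^6) = 0.51.
- p = 0.5, the largest possible q: 0.64 with k = 6, 0.53 with k = 5, 0.37 with k = 4.

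A subscale whose true score is zero cannot be missed, so k below 6 is to be expected in this population. About 0 to 0.5 point is a fair range.

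**Step 3: noisier ratings and rejections.** Simulation with latent scores rounded to ordinal levels, reference = subscale-wise maximum of the two ratings, and a share of ratings lowered by one level to mimic the rejection clause. Each cell gives the mean of raw minus reference, then the mean D from the best constant shift, without EEG.

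| Ratings lowered | Mean rater gap 1.1 | Mean rater gap 1.5 | Mean rater gap 1.9 |
|---|---|---|---|
| 0% | −0.99; +0.31 | −1.62; +0.63 | −2.18; +1.03 |
| 10% | −0.76; +0.13 | −1.30; +0.44 | −1.80; +0.67 |
| 20% | −0.46; 0 | −0.92; +0.21 | −1.39; +0.39 |
| 30% | −0.08; 0 | −0.49; 0 | −0.93; +0.16 |

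With no rejections, a linear rule on the rater's own six subscales gives much the same: +0.31, +0.67 and +1.02.

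**Step 4: would the test detect it?** A shift of c points confines D_i to the range from −c to +c, so its SD is far below the 2.5 assumed in 2.9; in the cells with a non-zero shift it was 0.5 to 1.0. At 98 participants, power for the shift alone is at least 99.8% across the 0% row. In the 20% row it is 2.5%, 85% and essentially 100%.

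**Step 5: do planned analyses separate the explanations?** A pure constant shift leaves Equation 5 equal to Equation 4, because |(T1 + c) − (T2 + c)| = |T1 − T2| away from the scale limits. It would therefore show no fall in inter-rater variability. A no-EEG model that shrinks scores would lower that variability, so this outcome cannot isolate EEG. The reduced mode in 2.10 still contains EEG.

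**The case against.** The best counter-argument is that the primary aim in 2.1 asks only whether AI totals lie closer to the adjudicated reference than single bedside totals do, and D_i tests exactly that. The objective concerns an integrated system and makes no separate claim for EEG. This stands: a positive D_i is a valid answer to the question as posed.

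Several stronger readings are tempting and are not supported.

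- **That every raw score is low by construction.** The rejection clause, the item-level rescoring and the credibility rules allow the reference to fall below a raw score. The shortfall holds on average only.
- **That the whole planned effect is an artifact.** That needs the noisiest setting and no rejections, or errors treated as continuous when the subscales are ordinal. Section 2.4.1 requires substantial pilot agreement between raters, which argues against the noisy end.
- **That the model will learn the offset.** Section 2.3 does not state how the retrospective training label is formed, so this is a possibility and not a fact.
- **That the Discussion claims to eliminate incorporation bias.** It says only that blinding should limit it. AI output does not enter the reference, and if experts anchored on the raw scores, that would favor the comparator and lower D_i.
- **That nothing planned could reveal a trivial rule.** Equations 4 and 5 would expose a pure constant shift, and Bland-Altman plots, subscale agreement and category agreement would help.

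What survives all of this is the missing contrast: no planned analysis compares the full model with one lacking EEG.

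**Conclusion.** The point holds as a limit on attribution. Reference, comparator and AI input share two assessments, and the highest-response rule places a single raw total below the reference on average unless rejections are common. A recalibration without EEG could then yield a positive mean D_i: roughly 0 to 0.5 point with one-level discrete errors, up to about 1.0 only with high noise and no rejections, and near 0 with frequent rejections. These sizes rest on assumed noise and rejection rates; the structural overlap rests on the text alone. A reader might infer that a positive primary result would be meaningless. It would not be: it would show that the locked output is closer to this reference than one raw score, but not that EEG is the reason.

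**What to change.** Keep the primary endpoint and the sample size. Before model lock, and from the same retrospective data, also lock:

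1. a fixed per-subscale offset added to the raw scores; and
2. the same architecture without EEG features.

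Prespecify as a secondary analysis the participant-level absolute-error difference of each comparator minus the full model, with bootstrap confidence intervals. Report the subscale-wise best-of-two raw score descriptively, noting that it uses both raters while each AI score uses one. Attribute error reduction to EEG only if the full model beats the no-EEG model. Reword the Discussion to say that blinding to AI output does not remove the overlap between reference, comparator and AI input.

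The cost is two extra locked models and a little more analysis, with no new patient data. The timing matters, because 2.3.5 bars updating during prospective validation and a comparator fitted after the reference scores are known would not be prespecified. The downside is that the EEG-attribution claim becomes harder to earn, and this contrast is not separately powered.

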### Inference workflow

2.6

The complete step-by-step prospective inference pipeline of the AI standardization system is outlined in Algorithm 1. Case-level explanations will be generated with a prespecified additive feature-attribution method after prediction. These explanations will support error review and model transparency but will not be described as part of the model architecture itself.

Algorithm 1Prospective inference workflow for AI-assisted CRS-R score standardization.

[figure not shown]

**Table 1 T1:** Operational CRS-R diagnostic mapping used by the rule-constrained integration layer.

Diagnostic category	Operational mapping rule
Coma	No eye opening and no reproducible CRS-R evidence of wakefulness or awareness, after excluding confounding sedation, paralysis, or acute medical instability
UWS/vegetative state	Wakefulness is present, typically with eye opening or sleep-wake cycling, but CRS-R items show no reproducible evidence of purposeful behavior meeting MCS or emergence criteria
MCS minus	Reproducible low-level but purposeful CRS-R behaviors are present, such as visual pursuit, fixation, localization to noxious stimulation, automatic motor response, or object manipulation that does not meet MCS plus criteria
MCS plus	Reproducible higher-order CRS-R behaviors are present, including command following, intelligible verbalization, or intentional communication that is not yet functional communication
Emergence from MCS	Functional communication or functional object use is present according to standard CRS-R rules

### Outcome measures

2.7

The primary outcome is the participant-level reduction in absolute CRS-R total-score error after AI-assisted standardization. For rater *j* of participant *i*, raw and AI-standardized absolute error, and participant-level paired difference are defined in Equations 1, 2, and3, respectively.

$$\begin{array}{l} \Delta_{ij}^{\text{raw}}=|T_{ij}^{\text{raw}}-T_{i}^{\text{ref}}|, \end{array}$$
(1)

$$\begin{array}{l} \Delta_{ij}^{\text{AI}}=|{\hat{T}}_{ij}-T_{i}^{\text{ref}}|, \end{array}$$
(2)

where $T_{i}^{\text{ref}}$ is the adjudicated reference total score.

The participant-level paired difference will be:

$$\begin{array}{l} D_{i}=\frac{1}{2}\overset{2}{\underset{j=1}{\sum }}\left(\Delta_{ij}^{\text{raw}}-\Delta_{ij}^{\text{AI}}\right). \end{array}$$
(3)

The primary analysis will test whether the mean of *D*_*i*_ differs from zero, with positive values indicating error reduction after AI-assisted standardization. This definition aligns the endpoint with the participant-level recruitment target while preserving both rater-specific observations.

Secondary outcomes include mean absolute error, root mean square error, agreement between AI-standardized and reference diagnostic category, agreement between standardized and reference subscale scores, reduction in inter-rater variability, sensitivity and specificity for detection of MCS and emergence from MCS, macro-averaged F1-score, uncertainty-flag performance, workflow feasibility, and exploratory consciousness improvement at day 14. Consciousness improvement will be defined as at least one ordered diagnostic-category improvement by day 14 compared with baseline. CRS-R total-score change at day 14 will be analyzed as a sensitivity metric. Discharge status and discharge timing will be reported descriptively rather than used as a primary prognostic time point.

Inter-rater variability for raw and AI-standardized total scores is calculated as specified in Equations 4 and 5.

$$\begin{array}{l} V_{i}^{\text{raw}}=|T_{i1}^{\text{raw}}-T_{i2}^{\text{raw}}|, \end{array}$$
(4)

$$\begin{array}{l} V_{i}^{\text{AI}}=|{\hat{T}}_{i1}-{\hat{T}}_{i2}|. \end{array}$$
(5)

### Error analysis

2.8

Prediction errors will undergo prespecified review. A serious prediction discrepancy event will be defined as an absolute difference of at least three CRS-R total-score points between the AI-standardized score and the adjudicated reference, or as a diagnostic shift across the UWS and MCS boundary. For such events, the study team will review input quality, EEG artifacts, rater disagreement, clinical confounders, model uncertainty, and prespecified feature-attribution summaries. The distribution of systematic errors across etiology, chronicity, airway status, sedation exposure, and severe motor impairment will be reported.

### Sample size

2.9

The retrospective development sample size will be justified separately from the prospective validation sample size, consistent with current guidance for clinical prediction model and AI model reporting (34, 37, 38). The final development report will state the number of unique patients, the number of assessment episodes, the number of episodes per patient, diagnostic-category frequencies, CRS-R subscale-level distributions, and the number of candidate and retained predictors. The model-development strategy will not rely on a simple events-per-variable rule. Instead, the final feature space and model complexity will be constrained through prespecified feature grouping, training-fold-only feature selection, penalization or tree-complexity limits when applicable, and patient-level nested cross-validation. Learning-curve or resampling summaries will be used to assess whether performance estimates remain unstable as development data are increased.

The prospective validation sample size is based on the participant-level primary endpoint. Assuming a mean participant-level reduction of 1.0 CRS-R point in absolute total-score error after AI-assisted standardization, a standard deviation of participant-level paired differences of 2.5, a two-sided alpha of 0.05, and 80% power, at least 98 evaluable participants are required. Allowing approximately 15% attrition due to unusable EEG, incomplete paired assessments, missing videos, or withdrawal, the planned recruitment target is 120 participants.

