### Statistical analysis

2.10

All analyses will be prespecified and performed after prospective database lock. The primary analysis population will include participants with two blinded bedside CRS-R assessments, usable EEG according to protocol, and an adjudicated reference score. A feasibility population will include all consented participants.

Baseline characteristics will be summarized as mean and standard deviation or median and interquartile range for continuous variables, and as counts and percentages for categorical variables. The primary analysis will summarize *D*_*i*_ and test whether the mean participant-level error reduction differs from zero using a paired test appropriate to the empirical distribution. A linear mixed-effects model with participant as a random effect and method and rater as fixed effects will be used as a secondary sensitivity analysis to estimate rater-level effects. Intraclass correlation coefficients, mean absolute error, root mean square error, and Bland-Altman plots will be reported with 95% confidence intervals.

Diagnostic-category agreement will be assessed with weighted kappa, macro-averaged F1-score, sensitivity, specificity, and confusion matrices using the mapping rules in Table 1. Subscale-level performance will be assessed using ordinal agreement metrics, weighted kappa, and subscale-specific absolute error. Inter-rater variability before and after AI-assisted standardization will be compared using paired tests and mixed-effects models. The uncertainty module will be evaluated by testing whether high-uncertainty cases are enriched for large scoring error, rater disagreement, or reference-standard disagreement.

Confidence intervals for primary and major secondary metrics will be estimated using participant-level bootstrap resampling. Prespecified subgroup analyses will explore model performance across etiology, chronicity, tracheostomy status, severe motor impairment, and recent sedative exposure. Sensitivity analyses will exclude participants with substantial clinical changes between ratings, cases exceeding target timing windows, and cases with major sedation or airway changes during the assessment episode. A reduced-feature inference mode using report-level EEG variables only will also be tested.

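### The 98 evaluable participants do not follow from the stated inputs: the paired endpoint needs about 52 for 80% power, and 98 gives about 97.5%

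*Protocol article*

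**What the plan says.** Section 2.7 (Outcome measures) averages the raw-minus-AI difference in absolute error over the two raters, which leaves one value, D_i, per participant. The primary analysis asks whether the mean of D_i "differs from zero, with positive values indicating error reduction after AI-assisted standardization". The section adds: "This definition aligns the endpoint with the participant-level recruitment target while preserving both rater-specific observations". Section 2.10 (Statistical analysis) repeats the aim: "test whether the mean participant-level error reduction differs from zero using a paired test appropriate to the empirical distribution".

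Section 2.9 (Sample size) ties the calculation to that endpoint: "The prospective validation sample size is based on the participant-level primary endpoint". The inputs are an effect of 1.0 ("Assuming a mean participant-level reduction of 1.0 CRS-R point in absolute total-score error after AI-assisted standardization") and "a standard deviation of participant-level paired differences of 2.5". The result is "a two-sided alpha of 0.05, and 80% power, at least 98 evaluable participants are required". After an allowance of about 15% for attrition, "the planned recruitment target is 120 participants".

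**The concern.** Every input to the calculation is printed, and so is the result, but the result does not follow from the inputs. The SD is already that of the within-participant differences, and the design contains no comparison of independent groups, so no factor of 2 belongs in the formula. The figure of 98 nevertheless looks like a one-sample requirement multiplied by 2.

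Two things are at stake. First, the article presents 98 as the minimum for 80% power in a population enrolled through representatives' consent. On the stated assumptions about half that number would do. Second, a reader cannot tell which element is wrong. If 98 and 80% are what the sponsor meant, then either the SD or the effect has been misstated; if the SD and effect are right, the power is misstated.

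**Working it through.** **Inputs** (section 2.9 unless noted)

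- Mean of D_i under the alternative: δ = 1.0
- SD of the paired differences: σ = 2.5
- Two-sided α = 0.05, so z = 1.960
- Power 80%, so z = 0.842
- Attrition about 15%; recruitment target 120
- Design: one D_i per participant, mean tested against zero (sections 2.7 and 2.10)

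**1. Reproducing the stated 98.** The per-group formula for two independent means is

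n = 2 × (z₀.₉₇₅ + z₀.₈₀)² × σ² / δ²

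- With rounded quantiles: 2 × (1.96 + 0.84)² × 6.25 / 1 = 2 × 7.84 × 6.25 = 98.0
- With unrounded quantiles: 98.11
- Power of a two-group comparison at 98 per group (normal approximation): 79.96%

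So 98 with 80% power is what a two-group trial would need in each group. That trial would have 2 × 98 = 196 participants and σ would be the SD within each group, not the SD of paired differences.

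**2. The formula that fits the endpoint.** For a one-sample (paired) test,

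n = (z₀.₉₇₅ + z₀.₈₀)² × σ² / δ²

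- Normal approximation: 49.06, rounded up to 50
- Exact noncentral t: power is 0.7999 at n = 51 and 0.8078 at n = 52, so 52

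**3. Can another paired analysis give 98?** Section 2.10 leaves the choice of paired test to the empirical distribution, so a signed-rank test is possible.

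| Variant, 80% power | Evaluable n |
|---|---|
| Paired, normal approximation, two-sided | 50 |
| Paired, exact t, two-sided | 52 |
| Signed-rank, relative efficiency 0.955 (52 / 0.955) | 55 |
| Signed-rank, worst-case relative efficiency 0.864 (52 / 0.864) | 61 |
| Paired, normal approximation, one-sided 0.05 | 39 |
| Stated in section 2.9 | 98 |

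None comes near 98.

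**4. What 98 delivers on the stated inputs** (exact t)

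- Power at n = 98: 97.5%
- Power at n = 120 × 0.85 = 102: 97.9%
- Effect detectable with 80% power at n = 98, SD 2.5: 0.715 points
- Largest SD that keeps 80% power for 1.0 point at n = 98: 3.495, close to 2.5 × √2 = 3.54, as an extra factor of 2 in the variance would imply
- Smallest significant mean at n = 98, if the observed SD is 2.5 and a t-test is used: t₀.₉₇₅,₉₇ × 2.5 / √98 = 0.50 points

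**5. Attrition step.** 98 / 0.85 = 115.3, so 116; a target of 120 covers it and would tolerate a loss of 1 − 98/120 = 18.3%. This step is sound given 98. Starting from 52, the same step gives 52 / 0.85 = 61.2, so 62 recruited.

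**The case against.** The strongest reply is that the error is harmless. It runs in the safe direction: the trial exceeds 80% power on its own assumptions, and the endpoint, the test and the type I error rate are untouched. If the SD of 2.5 proves optimistic, the surplus is useful. All of that is true, and it is why the numbers can stay. It does not make the printed statement correct: 98 is not the number required for 80% power under the inputs given.

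Several narrower points also stand. The article names no formula, so the two-group origin is an inference; with unrounded quantiles that formula gives 98.11, which strictly rounds up to 99. The mismatch does not depend on the origin. The ethics submission is not shown, so what the committee was told about the 98 is unknown. The 0.50-point figure is conditional on the observed SD and on a t-test, and it is partly a general feature of powered trials: at n = 52 the smallest significant mean would be about 0.70. Finally, 1.0 point is a planning assumption in the article, not a declared minimal important difference, so interpreting results against it would be a choice for the sponsor and does not follow from the arithmetic.

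That this is a condensed article is no answer, because nothing is missing: all inputs and the result are printed, and they disagree.

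**Conclusion.** The concern holds. With a mean D_i of 1.0, an SD of paired differences of 2.5, two-sided α of 0.05 and 80% power, the trial needs 50 evaluable participants by the normal approximation or 52 by the exact t, and at most about 61 if a signed-rank test is used. The stated 98 is nearly twice that (98 / 52 = 1.9), and the power at 98 is understated by about 17.5 percentage points. The conclusion rests only on the article's own inputs and on its definition of the endpoint as one paired difference per participant. The consequence is a wrong statement of sample size and power, not an underpowered trial. It should be corrected because the primary sample-size claim cannot be reproduced from its own assumptions.

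**What to change.** Correct the sample-size sentence in section 2.9. The simplest course keeps 98 evaluable and 120 recruited, for example:

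*With 98 evaluable participants, a two-sided one-sample t-test of D_i at α = 0.05 has 97.5% power for a mean reduction of 1.0 point if the SD of D_i is 2.5. As sensitivity information, the same number gives 80% power for a mean reduction of about 0.715 points at that SD, or for 1.0 point if the SD is as large as about 3.5.*

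The SD of 3.5 should be labelled as sensitivity information unless the sponsor has grounds to adopt it as the planning value.

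Alternatively, state the requirement as 52 evaluable (62 recruited at 15% attrition) and give a separate reason for recruiting 120, such as precision for secondary endpoints or subgroups. If 98 was derived from a different SD or effect, print those inputs instead.

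The cost is one or two sentences and no extra patients. Section 4 of the article says protocol modifications are reported to the ethics committee, so the correction would go there if it counts as one; the registry entry needs a matching change only if it carries the same justification.
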